## Background

Mixed urinary incontinence (MUI) is defined as a complaint of involuntary loss of urine associated with urgency, effort, or physical exertion or upon sneezing or coughing by the current International Continence Society guidelines [1]. The percentage of women suffering from the condition ranges from 14% to 61% [2]. It is regarded as urgency-predominant when a sudden sensation of voiding accompanied by uncontrolled incontinence is the dominant symptom [3]. Among women suffering from urinary incontinence (UI), about one-third have MUI with symptoms of both stress urinary incontinence (SUI) and urgency urinary incontinence (UUI) [4]. Urgency symptoms are more difficult to alter through lifestyle modifications or by controlling bladder activity than both stress-predominant MUI and balanced MUI symptoms [5, 6], resulting in more shame and inconvenience for women with urgency-predominant MUI. To relieve the symptoms, conservative treatments involving lifestyle interventions and behavioral and physical therapies are recommended by the European Association of Urology (EAU) guidelines, such as bladder training, electrical stimulation, and posterior tibial nerve stimulation. However, conservative treatments are often used as part of the treatment package because of uncertain effectiveness [4]. Other therapies for UI include surgical and pharmacological management. For urgency-predominant MUI, the success rate of surgery is 52%, 26% less than that for stress-predominant MUI [7]. Additionally, associated complications, adverse events and high costs also need to be considered when surgery is recommended. Solifenacin, the first-line medicine for urgency-predominant MUI, can reduce incontinence episodes in 24 h [8]. However, it can also induce common side effects of dry mouth, blurred vision, dry eyes, and constipation [4], and has a high medication discontinuation rate [9]. Consequently, alternative therapies with more effectiveness and safety urgently need to be explored.

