#### Patient recruitment

This study will be conducted in six hospitals over China, specifically Guang’anmen Hospital, China Academy of Chinese Medical Sciences; Jiangsu Province Hospital of Traditional Chinese Medicine; Shanxi Province Hospital of Traditional Chinese Medicine; Guangdong Province Hospital of Traditional Chinese Medical; the First Hospital of Hunan University of Chinese Medicine; and Hengyang Hospital Affiliated to Hunan University of Chinese Medicine. Of the six hospitals, one plans to recruit 42 patients, while the other five plan to recruit 48 patients each. Patients will be recruited via newspapers, posters, and networking both from the surrounding communities and hospitals. All potentially eligible women with incontinence will be invited to participate in the trial, proceeding with a series of history taking, physical examination, specialist diagnosis, questionnaire, voiding diary, and laboratory examinations to screen and enroll the patients, as recommended by EAU guideline [4]. Eligible patients will be randomly placed in the EA, SA, or solifenacin treatment group.

Demographic information about age, marital status, menstrual status, education background, occupation, and medical history will be cautiously recorded at the baseline period. The International Consultation on Incontinence Questionnaire Short Form (ICIQ SF) and the Overactive bladder questionnaire short form (OAB-q SF) will also be used at the baseline period to assess the severity of incontinence symptoms and the influence on quality of life (QoL).

In the EA and SA groups, patients will receive 12-week treatment and 24-week follow-up, while those in the solifenacin treatment group will take the medicine for a succession of 36 weeks. Assessments will be carried out at the baseline, at 4, 8, and 12 weeks from the baseline in the treatment period, and at 24 and 36 weeks from the baseline in the follow-up period (Fig. 1 Study Flowchart; Table 1 Outcome Assessment Schedule).

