#### Safety assessment

##### Side effects associated with acupuncture

Unintended events and feelings related to EA and SA will be recorded in the CRF, including broken needles, fainting, bleeding, bruising, infection and aposteme, unbearable ache (VAS ≥ 8), vomiting, nausea, palpitations, dizziness, headache, anorexia, and insomnia.

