##### Side effects associated with solifenacin

The side effects induced by Solifenacin will be recorded in the CRF, including dry mouth, dry eyes, and constipation.

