##### Adverse events

Except from the side effects induced by EA, SA, and solifenacin, all other adverse events will be recorded in the CRF throughout the trial, and their relationships with the intervention and controls will be assessed.

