### Statistical analysis

For the primary hypothesis, we will compare the decrease in UUI episodes among the three groups. A decrease in number will indicate less incontinence. Additionally, we will use a modified *t*-test based on the retention of effect method to analyze whether EA is noninferior to solifenacin [21]. In detail, to establish the assay sensitivity of the trial, a *t*-test investigating the superiority of solifenacin over SA will be performed first by comparing the decrease in the number of UUI episodes in the solifenacin and SA groups. After superiority has been established, a modified *t*-test will be used to assess whether the difference in the numbers between the EA and SA groups is more than 50% of the mean difference between the numbers in the solifenacin and SA groups. An appropriate Fieller’s confidence interval can also be provided [21]. If the *P* Value is equal to or less than 0.025 or if the lower boundary of the confidence interval around the mean difference between the numbers in the EA group versus that in the solifenacin group exceeds this value, then noninferiority will be established. After the noninferiority assessment, traditional *t*-tests will be used for superiority analyses, including a decrease in the number of UUI episodes for solifenacin versus EA, and EA versus SA.

A mixed-effect model or Wilcoxon rank-sum test will be used to assess the longitudinal continuous variables. A generalized linear model or logistic regression will be performed to assess the rates of response. Chi-square or Fisher’s exact tests will be used to compare the frequency of AEs between groups.

Primary outcome analysis will be performed in the intention-to-treat (ITT, randomized participants) and per-protocol datasets (PP, ITT participants who received at least one treatment session without major violation of the protocol). Missing data will be imputed using the multiple imputation method under the missing-at random assumption. Secondary and safety outcomes will be assessed in ITT populations.

Since all analyses other than the primary analysis are considered descriptive, no adjustments will be made for multiple testing, and *P* values should be interpreted accordingly. Analyses will be performed using SAS version 9.4 (SAS Institute Inc) with a two-sided *P* value of less than .05 considered significant.

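### The crude test of adverse-event frequency is not like-for-like for EA or SA versus solifenacin: named side-effect lists, treatment contacts and time on treatment all differ

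*Protocol article*

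**What the plan says.** All references are to the protocol article.

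- **Test.** Under Statistical analysis, Chi-square or Fisher's "exact tests will be used to compare the frequency of AEs between groups". The same section adds: "Secondary and safety outcomes will be assessed in ITT populations". It gives no time window, no exposure adjustment and no restriction of which groups are compared. It labels every analysis other than the primary one descriptive.
- **Acupuncture side effects.** "Unintended events and feelings related to EA and SA will be recorded in the CRF", followed by 13 examples. Some are tied to needling (broken needles, bruising). Others could occur in anyone (nausea, dizziness, headache, palpitations, insomnia).
- **Solifenacin side effects.** "The side effects induced by Solifenacin will be recorded in the CRF, including dry mouth, dry eyes, and constipation". The Background says of the same drug that "it can also induce common side effects of dry mouth, blurred vision, dry eyes, and constipation".
- **Everything else.** Under Adverse events, "all other adverse events will be recorded in the CRF throughout the trial, and their relationships with the intervention and controls will be assessed".
- **Duration.** Under Patient recruitment, both acupuncture arms are treated for 12 weeks and then followed for 24 more. For the drug, the same section states that "those in the solifenacin treatment group will take the medicine for a succession of 36 weeks". Assessments at weeks 4, 8, 12, 24 and 36 are common to all arms. Table 2 gives EA and SA the same 36 sessions over 12 weeks.

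**The concern.** A test of crude event proportions compares treatments fairly only if events are looked for in the same way and the period counted suits the question. Here the drug arm differs from both acupuncture arms in what is named for recording, in how often staff see the woman, and in how long she is treated. Any of these can move the count without a difference in how well the treatments are tolerated.

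This matters because the Background motivates the trial partly by solifenacin's side effects and discontinuation rate, and calls for alternatives that are safer as well as more effective. Readers will therefore look at acupuncture versus drug in the adverse-event table. Efficacy is judged at week 12, but no matching window is set for safety.

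**Working it through.** The plan gives no adverse-event rate, so there is no figure of its own to reproduce. The check sets the recording features side by side and then shows what they could do to the planned test.

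**Step 1: the arms compared**

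| Feature | EA | SA | Solifenacin |
|---|---|---|---|
| Named side effects | 13 | same 13 | 3 |
| Treatment sessions, weeks 0–12 | 36 | 36 | none described |
| Shared assessments (weeks 4, 8, 12, 24, 36) | 5 | 5 | 5 |
| Weeks on treatment | 12 | 12 | 36 |
| Weeks observed | 12 + 24 = 36 | 36 | 36 |

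The count of 13 takes infection and aposteme as one item. There are two recording schemes, and the split runs between acupuncture and drug.

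**Step 2: EA versus SA**

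With n = 94 per arm, two-sided 0.05 and equal true rates of 5%, 10% or 20% (assumed), exact enumeration of Fisher's test gives false-positive rates of 2.0%, 2.8% and 3.4%. All are below 5%, and nothing in the recording scheme distorts this contrast.

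**Step 3: exposure alone, acupuncture versus solifenacin**

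Assume the same constant weekly hazard while on treatment in both arms, and no treatment-related events once treatment ends. A 12-week risk p then becomes 1 − (1 − p)³ over 36 weeks. For p = 0.10, 1 − 0.90³ = 0.271.

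| 12-week risk (assumed) | 36-week risk | Fisher rejects | Normal approximation |
|---|---|---|---|
| 2% | 5.9% | 14% | 28% |
| 5% | 14.3% | 49% | 58% |
| 10% | 27.1% | 83% | 86% |
| 15% | 38.6% | 95% | 96% |

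These rejections reflect a real difference in cumulative risk between regimens. They are wrong only if read as a difference in tolerability per week of treatment.

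**Step 4: capture alone**

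Assume the same true incidence in both arms, with full capture in the acupuncture arm and a share s captured in the drug arm.

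| True incidence (assumed) | s = 50%: Fisher rejects | s = 75%: Fisher rejects |
|---|---|---|
| 10% | 18% | 6% |
| 20% | 41% | 11% |
| 30% | 64% | 17% |

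**Step 5: both together**

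Take a 12-week risk of 10% and s = 50%. Over weeks 0–12 the table would show 10% on acupuncture and 0.50 × 10% = 5% on drug. Over 36 weeks it would show 10% and 0.50 × 27.1% = 13.6%. The same underlying hazard makes acupuncture look worse in one window and the drug look worse in the other.

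**The case against.** The strongest reply is that the safety scheme is more complete than the two lists suggest. Both lists are open-ended, and the Adverse events section records all other events in every arm throughout the trial, with relationship assessed. A headache on solifenacin, constipation on EA or blurred vision on the drug can therefore all be recorded. This stands: no event is shut out. It does not make recording equal, because an item named on the form is more likely to be captured than one left to a residual category.

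Several stronger readings are tempting, and the document does not support them.

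- *Every arm has its own scheme, so the whole safety comparison is biased.* EA and SA share the list, the sessions and the follow-up, and patients in both are blinded.
- *Women are actively asked about 13 items in one arm and 3 in the other.* The text says that events are recorded. It describes no questioning and does not say that events are reviewed at each session.
- *Unequal exposure is itself bias.* All arms are observed for 36 weeks, so comparing whole regimens over that time is a legitimate question.
- *Analysing safety in the ITT set is a fault of the same weight.* No number of untreated or switched women is given or implied, so no size can be attached to it.

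The descriptive label also stands: no confirmatory safety claim is planned. But P values are still to be produced, and the label does not cure unequal recording. An unseen SAP may define windows and contrasts, but it cannot recover symptoms that were not recorded evenly.

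**Conclusion.** The point holds for EA versus solifenacin and SA versus solifenacin only. As written, the plan applies a crude frequency test to arms that differ in named items (13 versus 3), in treatment contacts (36 sessions versus none described beyond the shared assessments) and in time on treatment (12 versus 36 weeks).

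The possible size ranges from negligible to large: Fisher rejection in 14% to 95% of trials from exposure alone, and 6% to 64% from capture alone. These figures rest on assumed event rates, a constant hazard and assumed capture shares, since the document gives none of them. Longer treatment raises the drug count, while a longer list and more contact raise the acupuncture count, so the net direction cannot be stated.

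The consequence is for interpreting relative safety. The primary efficacy analysis and the EA–SA safety contrast are unaffected. A reader might infer that any safety difference from solifenacin will be an artefact. The document does not support that; it supports only that such a difference could not be cleanly attributed.

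**What to change.** 1. Record one symptom list in all three arms at the visits they already share (weeks 4, 8, 12, 24 and 36). The list is the union of the two existing lists plus blurred vision: 13 + 3 + 1 = 17 items.
2. Report a weeks 0–12 adverse-event comparison beside the 36-week whole-regimen comparison, and label each with the question it answers. Which of the two leads is a choice of estimand for the sponsor.
3. Report needle-specific events for EA and SA only, without a test against solifenacin.

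The cost is a small case report form change and a few lines of analysis wording; no visits are added. The Trial status section says that recruitment has started, so women already past a visit will lack the common list there. The report should say how many that is.

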## Methods and analysis

### Study design

The study will be a multicentered, randomized, three-armed, non-inferiority clinical trial with sham electroacupuncture (SA) and solifenacin as controls. The null hypothesis is that the improvement (difference in the number of UUI episodes between baseline and 12-week assessment) in the EA group would be 50% or less of the difference in improvement between the solifenacin and SA groups; that is, noninferiority would be established if EA, compared with solifenacin, retains at least 50% of the efficacy of solifenacin over SA. The outcome assessors and statisticians will be blinded. Patients in the EA and SA groups will be blinded, while those in the solifenacin group will not be blinded. The study will be carried out after the ethics is approved by the Institutional Review Board. All the patients in the study will be informed about the details of the study and written informed consent will be obtained before enrollment.

In the written informed consent, the participants will be informed that if they are eligible and willing to participate in the study, they will be randomized into the EA group, SA group, or solifenacin group with the same probability. The investigators plan to enroll 282 participants, with 94 in each group. Solifenacin is an effective treatment for the UUI component, as recommended by the current guidelines, and our previous studies indicated that EA and SA are both effective for urgency-predominant MUI to some degree. In the EA group, participants will receive traditional EA at traditional acupoints, while participants in the SA group will receive shallow and minimal EA at non-acupoints.

The study is designed and reported in accordance with the Consolidated Standards of Reporting Trials (CONSORT) guidelines, the Standard Protocol Items: Recommendations for Interventional Trials (SPIRIT) Checklist, and Standards for Reporting Interventions in Controlled Trials of Acupuncture (STRICTA) recommendations. The protocol has been reviewed, revised, and supported by experts in statistics, urology, and acupuncture.

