#### Concomitant treatment

To avoid other influences on the function of the lower urinary tract and incontinence symptoms, patients will be recommended not to receive any other treatments. If used, the treatment or medication should be clearly recorded in the CRF.

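### Safety is to be analysed in all randomised women, so any who never start treatment would count in the adverse-event denominators; a treated set is better

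*Protocol article*

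**What the plan says.** All of this is in the protocol article, mainly under Statistical analysis.

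- The analysis set for harms is named: "Secondary and safety outcomes will be assessed in ITT populations".
- Intention-to-treat (ITT) is defined in the same paragraph by two words only, "ITT, randomized participants". Having started treatment is not required.
- The per-protocol set does require it: "PP, ITT participants who received at least one treatment session without major violation of the protocol". That set is planned for the primary outcome only.
- The between-arm comparison is stated: "Chi-square or Fisher’s exact tests will be used to compare the frequency of AEs between groups".
- Under Study design and Blinding, women in the EA and sham (SA) arms do not know which they receive, whereas "those in the solifenacin group will not be blinded".

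No other section defines a safety or as-treated population.

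**The concern.** ITT preserves the randomised comparison for efficacy. For harms it has a known drawback, because people who were never exposed enter the denominator. The two side-effect sections list events tied to needling or caused by solifenacin, and these cannot occur without exposure. Each woman who never starts therefore adds one to the denominator and nothing to the numerator, and the rate is understated.

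The per-protocol definition shows that ITT here can include such women. Its condition of at least one session would be redundant if ITT already carried it.

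Non-start may also differ between arms. A woman allocated to solifenacin learns this at once and may decline, while a woman allocated to EA or SA does not know which she has. The Background motivates the trial partly by solifenacin's side effects and the wish for a safer alternative, so readers will use the between-arm comparison of adverse events.

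**Working it through.** **What can be reproduced.** The article has no calculated safety figure to reproduce. The planned denominator is consistent: "The investigators plan to enroll 282 participants, with 94 in each group", and 3 × 94 = 282. The hospital quotas under Patient recruitment agree: 42 + 5 × 48 = 282. The ITT safety denominator is thus 94 per arm.

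**Inputs the article does not give.** It states neither an adverse-event rate nor a share of women who never start. Both are assumed below. The only related figure is the 10% expected drop-out under Sample size calculation, which covers all drop-out. I use never-start shares of 2%, 5% and 10%. The last would mean that all the planned drop-out happens before the first session or dose. The 10% is a planning figure for the whole trial and not a ceiling for any one arm.

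**Dilution within an arm.** Let p be the rate in treated women and d the share who never start, with no events in those who never start. Then

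ITT rate = p × (1 − d), and the relative understatement equals d.

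| Rate in treated women | d = 2% | d = 5% | d = 10% |
|---|---|---|---|
| 5% | 4.9% | 4.75% | 4.5% |
| 10% | 9.8% | 9.5% | 9.0% |
| 20% | 19.6% | 19.0% | 18.0% |
| 30% | 29.4% | 28.5% | 27.0% |

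The absolute loss runs from 0.1 to 3.0 percentage points. In counts: if 9 of 94 women never start and 17 of the 85 treated have the event, the rate is 17/85 = 20.0% in treated women and 17/94 = 18.1% under ITT.

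The formula fits treatment side effects. A woman who never starts can still have an unrelated adverse event, so for all-cause events the dilution is smaller.

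**Between arms.** Assume rates in treated women of 20% on solifenacin and 5% on EA, a true difference of 15.0 points.

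- Non-start 10% in both arms: 18.0% − 4.5% = 13.5 points; the ratio stays at 4.0.
- Non-start 10% on solifenacin, none on EA: 0.20 × 0.90 − 0.05 = 13.0 points; the ratio falls to 18/5 = 3.6.
- Non-start 10% on EA, none on solifenacin: 0.20 − 0.05 × 0.90 = 15.5 points.

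In the case the open label makes most plausible, the second, the distortion runs against EA.

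**Power.** For 20% against 5%, two-sided 0.05, with 10% non-start in both arms, power is 84.5% in treated women (84.6 per arm) and 83.9% under ITT (94 per arm, 18.0% against 4.5%). The choice of set affects the reported rate, and hardly affects the chance of a significant test.

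**The case against.** The best case for leaving the sentence alone has four parts.

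1. **Non-start may be rare.** Women consent knowing they may get any of the three arms, those with contraindications to solifenacin or intolerance of EA are excluded, and randomisation follows confirmed eligibility. This stands: non-start, and more of it in the open arm, is a possibility that the article does not quantify.
2. **The stakes are low.** The stated hypothesis concerns urgency incontinence episodes, and the article calls every analysis other than the primary one descriptive. This also stands and limits the weight of the point.
3. **A treated set has its own cost.** It depends on an event after randomisation. If women leave the open arm on learning their allocation, removing them alters that arm selectively. This is a fair trade-off, and the reason to keep the ITT analysis as support.
4. **The detail may be in the full plan.** This does not stand. The article names the safety population and defines it, so a later plan with a treated set would contradict it.

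A reader might infer more: because other treatments are only discouraged ("patients will be recommended not to receive any other treatments"), side effects of a drug added by a woman in the EA or SA arm would be charged to acupuncture. The article does not support that. It records events related to needling separately from those caused by solifenacin, assesses the relationship of other adverse events to the interventions, and records any other treatment used. No crossover is planned. A treated set would not change the matter either: a woman who had EA sessions and added a drug has still received EA.

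**Conclusion.** The point holds as a minor one. By its own definitions the plan puts women who were never treated into the denominator of the side-effect rates, and no safety analysis is restricted to women who were exposed.

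The relative understatement equals the never-start share. On the assumed shares of 2% to 10%, a 20% rate loses 0.4 to 2.0 points, and with no non-starters the loss is zero. The sizes rest on assumed event rates, assumed shares, and no treatment side effects in women who never start.

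A reader might take this as a bias that flatters EA, or as one already shown to exist. Neither follows. The article does not say that any woman will fail to start, and extra non-start in the open solifenacin arm would make solifenacin look safer and shrink any advantage of EA. The primary non-inferiority conclusion is unaffected.

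**What to change.** Replace the sentence on secondary and safety outcomes with:

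> Secondary efficacy outcomes will be assessed in the ITT population; safety outcomes will be assessed in all participants who received at least one session or one dose, grouped by treatment received, with the ITT safety analysis as supportive.

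The cost is one sentence and no new data. Sessions are recorded (Adherence assessment), as are the solifenacin dose taken (Table 1) and its changes and discontinuation (Solifenacin treatment group). Table 1 first records the dose at week 4, so state how a woman lost before then is classed. Also report the number in each arm who never started, so that readers can see whether the two analyses could differ.

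The downside is a small departure from the randomised comparison, which the supportive ITT analysis covers. Recruitment has already started, so the change should be made before safety data are examined by arm.

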## Abstract

**Background:**

Among women suffering from urinary incontinence (UI), about one-third are diagnosed with mixed urinary incontinence (MUI), among which urgency-predominant MUI causes more shame and inconvenience to patients. The treatments for urgency-predominant MUI have limited guidelines and previous studies have indicated that electroacupuncture (EA) might be a safe and effective option. The present study aims to evaluate the effect of EA on women with urgency-predominant MUI.

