Acupuncture might be a promising candidate for the treatment of urgency-predominant MUI. As previous research has indicated, electroacupuncture (EA) might be noninferior to pelvic floor muscle training (PFMT) plus solifenacin in reducing urgency incontinence episodes for women with MUI [10]. However, the trial included patients with stress-predominant MUI, urgency-predominant MUI, and balanced MUI rather than focusing on urgency-predominant MUI exclusively; hence, it is difficult to confirm whether EA is effective for the treatment of urgency-predominant MUI. In addition, the efficacy of EA cannot be clearly illustrated because of the lack of a sham acupuncture-controlled group. For this reason, the present study is a three-armed sham-controlled randomized trial aimed at evaluating the effects of EA and comparing the effects of EA and solifenacin in reducing urgency incontinence episodes for women with urgency-predominant MUI.

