## Discussion

This study aims to demonstrate that EA is noninferior to solifenacin in reducing UUI episodes in women with urgency-predominant MUI after 12-week treatment.

At present, the diagnostic criteria for urgency-predominant MUI have not been clearly defined. In this study, women will be diagnosed with MUI through history taking, physical examination, questionnaires, voiding diary, specialist diagnosis, and laboratory tests as recommended by the 2018 EAU guidelines. The MESA questionnaire and 3-day voiding diary will be applied to doubly ensure urgency-predominance, which needs to be studied further.

Voiding diaries of 3 and 7 days are reliable in monitoring changes in voiding and incontinence and are thus used as the main tools for outcome assessment. Since urgency is a bothersome symptom in urgency-predominant MUI, overactive bladder, PPIUS, and OAB-q SF are applied to evaluate the severity and the influence on QoL. In this study, both subjective and objective measurements will be applied to assess the outcomes.

In two-arm non-inferiority trials, the choice of a non-inferiority margin is usually based on differences between the active comparator and placebo from previous trials and meta-analyses [22]. However, this approach is problematic for this study because the active comparator in the trial will not necessarily have the same efficacy as previous results in the literature.

A two-arm non-inferiority trial in which a placebo arm is not included is not appropriate due to the lack of assay sensitivity.

The non-inferiority design with a three-arm trial allows indexing of the therapeutic effect of EA based on the performance of Solifenacin and SA within the trial, instead of using external references, as further discussed. Therefore, it is considered the “gold standard” of non-inferiority trials according to the US Food and Drug Administration (FDA) and the European Medical Agency (EMA) [23].

However, the placebo of Solifenacin is rather difficult to access in China, making the blinding of all patients impossible in a three-armed non-inferiority trial. Therefore, the efficacy of solifenacin (solifenacin plus SA) compared with a placebo (Placebo plus SA) cannot be assessed.

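### EA versus sham is a stated aim but has no confirmatory place of its own; efficacy is confirmed only indirectly, when the solifenacin and retention steps both succeed

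*Protocol article*

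**What the plan says.** **The aim.** The Abstract (Background) says: "The present study aims to evaluate the effect of EA on women with urgency-predominant MUI". The main Background section faults the earlier trial because "the efficacy of EA cannot be clearly illustrated because of the lack of a sham acupuncture-controlled group". It gives this as the reason for a three-arm sham-controlled trial "aimed at evaluating the effects of EA and comparing the effects of EA and solifenacin". The Discussion gives SA a second role, since the three-arm design "allows indexing of the therapeutic effect of EA based on the performance of Solifenacin and SA within the trial", and there the aim is non-inferiority alone: "This study aims to demonstrate that EA is noninferior to solifenacin in reducing UUI episodes".

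**The tests.** The Statistical analysis section opens with a comparison of all three groups under the primary hypothesis and then sets an order:

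1. Solifenacin superior to SA, to establish assay sensitivity.
2. Only once that is shown, a modified t-test of whether EA–SA exceeds 50% of solifenacin–SA, at P of 0.025 or less.
3. After the non-inferiority assessment, ordinary t-tests "for superiority analyses, including a decrease in the number of UUI episodes for solifenacin versus EA, and EA versus SA".

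The section then says: "Since all analyses other than the primary analysis are considered descriptive, no adjustments will be made for multiple testing". It does not list the contrasts that make up the primary analysis, and it does not say what becomes of EA versus SA if solifenacin fails to beat SA.

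**The concern.** The comparison that would answer the first-listed aim stands third in the order, beside solifenacin versus EA, under a clause that makes everything outside the primary analysis descriptive. It is also the only contrast in which patients are blinded in both arms (Blinding section). Its confirmatory value hangs on a test against an open-label drug arm and on a retention test that needs a much larger effect to succeed.

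If either of those steps fails, the trial could show a clear difference between EA and sham and still have no confirmatory statement to make about it. Failure of the solifenacin step cannot be ruled out: the Study design section says "our previous studies indicated that EA and SA are both effective for urgency-predominant MUI to some degree", which narrows the room for solifenacin to beat SA.

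**Working it through.** **Inputs from the article.** 282 women, 94 per group, 1:1:1; 10% drop-out; 50% retention; 0.025 for non-inferiority (taken as one-sided) and two-sided 0.05 elsewhere. Evaluable per arm: 94 × 0.9 = 84.6, taken as n = 85.

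**The plan's own figure.** 3 × 94 = 282 and 42 + 5 × 48 = 282, so the totals agree. The sample size itself cannot be reproduced, because the article gives no effect size, SD or power.

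**Assumptions.** Effects over SA in SD units, a common known SD, normal means. The effect sizes are mine.

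**Rejection rules** (E, R and S are the mean decreases on EA, solifenacin and SA):

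- Solifenacin step: R − S > 1.96 SD √(2/n)
- Retention step: E − 0.5R − 0.5S > 1.96 SD √(1.5/n), since 1 + 0.25 + 0.25 = 1.5
- EA over SA: E − S > 1.96 SD √(2/n)

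**What follows when both steps pass.** E − S = (E − 0.5R − 0.5S) + 0.5(R − S). Passing both steps therefore forces

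E − S > 1.96 (√1.5 + 0.5√2) SD/√n = 1.96 × (1.225 + 0.707) SD/√n = 1.96 × 1.93 SD/√n.

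EA over SA needs only 1.96 × 1.41 SD/√n. At n = 85 that is 0.41 SD against 0.30 SD. The implication does not need equal arms or equal variances: the standard error of a sum never exceeds the sum of the standard errors, so it holds under the normal approximation if all three tests use the same variance estimates.

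**How often the answer is lost.** Simulation at n = 85, 1,000,000 trials per row:

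| Solifenacin / EA effect (SD) | EA beats SA | Both steps pass | EA beats SA, at least one step fails | EA beats SA, solifenacin step fails |
|---|---|---|---|---|
| 0.4 / 0.4 | 74.1% | 24.1% | 50.0% | 13.2% |
| 0.5 / 0.5 | 90.3% | 42.4% | 48.0% | 6.6% |
| 0.2 / 0.5 | 90.4% | 21.8% | 68.5% | 65.2% |
| 0.75 / 0.75 | 99.8% | 80.5% | 19.4% | 0.2% |

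In no simulated trial did both steps pass without EA also beating SA. When the two treatments are equally effective, most of the loss comes from the retention step. When solifenacin is weak, most of it comes from the solifenacin step.

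**The case against.** The strongest reply is that this is a non-inferiority trial. The title, the null hypothesis, the margin and the Discussion all say so; testing assay sensitivity first suits that question; and SA is there partly to supply it. That stands as an account of the primary question. It does not remove the other role that the Background section gives to SA.

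Two stronger readings are tempting, and the documents do not support them.

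- *EA efficacy gets no confirmatory answer at all.* When both steps pass, EA over SA follows at controlled error, as shown above.
- *The sequence stops before EA is compared with SA if solifenacin fails.* Only the retention test is made conditional on success. The EA–SA t-test is placed after the non-inferiority assessment, which sets an order and does not cancel the test.

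The descriptive status is itself an inference. The primary analysis is not tied to named contrasts, the section opens with a three-group comparison, and an analysis plan that is not shown may settle the matter. This limits the point to the natural reading. Under the other reading EA versus SA would be primary, yet with no stated place in the hierarchy or share of alpha, and that also needs correcting.

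The 0.2/0.5 scenario favours the concern, because it gives EA 2.5 times the effect of solifenacin. An active sham shrinks EA–SA as well as solifenacin–SA, and the article calls solifenacin effective. The equal-effect rows are the fairer guide; there the solifenacin step alone accounts for 13% or less, and the larger loss comes through the retention step.

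**Conclusion.** The point holds in this form: evaluating EA's effect is a stated aim for which sham was added, but EA versus SA has no named confirmatory place and is most naturally read as descriptive. The aim is answered with confirmatory weight only through the joint success of the solifenacin and retention steps.

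Under equal effects of 0.4 to 0.5 SD, about half of all trials would show EA beating SA without that joint success. The share falls to about 19% at 0.75 SD and rises to about 69% if solifenacin is weak (0.2) and EA is not (0.5). These sizes rest on assumed effects, 85 evaluable per arm and a normal approximation with a common SD. The conclusion about the status of the test rests on the text alone.

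**What to change.** In the Statistical analysis section, define the primary analysis as a fixed sequence:

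1. EA over SA, two-sided 0.05.
2. Solifenacin over SA, two-sided 0.05.
3. The 50% retention test, one-sided 0.025.

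State that step 1 stands on its own if a later step fails, and keep solifenacin versus EA superiority descriptive. Align the aim in the Discussion with the Abstract and Background, and carry the same order into the analysis plan.

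**Cost.** A wording change with no extra patients or data. Recruitment has started, so it should be a dated amendment made before unblinding. The fixed order controls type I error without splitting alpha. By contrast, adding EA versus SA as a second unadjusted 0.05 family could raise the error rate to 1 − 0.95² = 9.75% under independence. Non-inferiority loses no power, because passing steps 2 and 3 already implies passing step 1. The one thing given up is that solifenacin over SA would not be confirmatory in a trial where EA does not beat SA; the plan uses that test only as the gate to retention, which would fail in such a trial in any case.
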